### Secondary endpoints

Secondary endpoints are:

Time to first occurrence of all-cause mortality or hospitalization for heart failure.Time to first occurrence of all-cause mortality.Time to first occurrence of hospitalization for heart failure.Time to first occurrence of AF *de novo* and AF burden at every follow-up visit.The echocardiographic change in LVEF at 1 year as compared to baseline.The echocardiographic changes in diastolic (dys-)function at 1 year as compared to baseline.The occurrence of pacemaker-related complications.QOL assessed by the EQ-5D-5L questionnaire.Cost-effectiveness analyses and budget impact analysis (BIA).

The secondary endpoints (other than echocardiographic endpoints) will be determined at the end of the follow-up period when the last included patient has reached 1-year follow-up. The individual follow-up time for patients at this time point will vary, with a minimum of 1 year and a maximum of 36 months.

### Adjudication of endpoints

All clinical endpoints as described above are adjudicated by an independent, blinded endpoint adjudication committee (EAC). The EAC consists of three experienced cardiologists. Two of them adjudicate all clinical endpoints. In case of disagreement, after discussion with the third committee member, they decide on the adjudication of the endpoint. All endpoints are adjudicated using standardized definitions provided in the EAC charter.

An independent echo core lab, composed of two experienced imaging cardiologists, assesses all baseline and follow-up TTE’s. Based on the baseline and 1-year follow-up LVEF, as assessed by the echo core lab, the echocardiographic part of the primary endpoint is determined. The echo core lab is blinded for the study number and date of the examination. Due to the presence of pacing leads, the core lab cannot be completely blinded to the allocation of the patient.

An ECG core lab, consisting of two experienced LBBAP implanters, assesses all paced baseline and 1-year follow-up ECG’s to determine the presence of RVP, deep septal pacing, or LBBAP according to the previously published definition.^9^ Capture of the left-sided Purkinje system is determined according to the current consensus.^9^

## Analyses

### Sample size calculation

Based on previously reported mortality, heart failure hospitalizations, and significant deterioration of LVEF,^2,6–8,22^ we estimate that the proportion of patients in the RVP group that will develop any of the composites of the primary endpoint before 1-year follow-up will be at least 25%. We expect an event rate of 14% for the LBBAP group. Event rates are based on the effect size of heart failure-related events by his pacing in those with ventricular pacing percentage >20%.^6^ When designing this trial, no data on event rates in LBBAP were available yet. The effect size of LBBAP was estimated to be equal to HBP when designing this trial. To achieve a power of 80% at the 5% level of significance, 203 patients per group, or 406 in total, would be needed. Accounting for around 15% loss to follow-up or patients not receiving the allocated intervention, 470 patients are needed.

After designing the trial, Sharma et al. reported an occurrence of the combined primary clinical endpoint of mortality, heart failure hospitalization, or upgrade to CRT among patients with ventricular pacing burden > 20%, in 26.1% in RVP and 8.4% in LBBAP after a mean follow-up of 1.5 years in a non-randomized trial (HR 0.32; 95% CI 0.19–0.54; *P* 0.001).^15^ This study included a longer follow-up duration but excluded the echocardiographic endpoint. The addition of the echocardiographic endpoint in the LEAP trial will generate more endpoints in a shorter follow-up duration. Therefore, the study by Sharma et al. is substantiating the sample size calculation.

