### Randomization, blinding, and treatment allocation

Patients are randomized in a 1:1 ratio via an interactive response technology system by block randomization. Random permuted block sizes will be used to prevent prediction of treatment allocation before randomization. Randomization will be stratified by sex and percentage of LVEF (i.e. LVEF <50% and LVEF ≥50%) to ensure an even distribution of these characteristics between the two treatment groups. Given the nature of the treatment arms, the participating patients and treatment team are not blinded. Adjudication of the endpoints is performed by a blinded committee.

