## Study procedures

### Intervention group

The intervention group is treated with LBBAP. LBBAP consists of the implantation of a pacemaker with the ventricular lead delivered through the interventricular septum to the LV septum, targeting capture of the LBB. However, if it is not possible to capture the LBB, LVSP is considered adequate as well.^9^ The feasibility and safety of this implantation method have been described previously.^13,14,20^

In case of unsuccessful lead positioning in the LBBAP region, the lead may be placed at the His bundle region or in the right ventricle according to the physician’s discretion.

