### Statistical analyses

Analyses will be executed on an intention-to-treat population. This population includes all patients who are randomized, regardless of the treatment they received. For example, all patients randomized to LBBAP and not receiving LBBAP (i.e. RVP or HBP) will be analysed according to their randomization group (thus LBBAP). The same counts for all patients randomized to RVP and not receiving RVP.

Given the possibilities of crossovers, as a secondary analysis, an exploratory per-protocol analysis will be performed to check for consistency and explore potential efficacy. The per-protocol analysis will include all patients randomized to LBBAP who received LBBAP and all patients randomized to RVP who received RVP.

The ECG corelab will assess all paced baseline and 1-year follow-up ECGs to determine the pacing type the patients are treated with. Descriptive statistics (i.e. count (%)) will be used to display the actual pacing types (i.e. RVP, LBBAP, or HBP) in both treatment groups.

Categorical baseline characteristics will be presented as count (percentage). Continuous characteristics will be presented as mean (± standard deviation) or median (interquartile range) as appropriate.

All primary and secondary study endpoints will be described in detail as count and percentage (binary endpoints), using Kaplan–Meier curves (time-to-first occurrence of an endpoint), Cox regression analysis, and as mean and standard deviation (continuous endpoint, i.e. LVEF), depending on the type of outcome. All null-hypothesis testing will be performed using a level of significance of α = 0.05.

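### The 15% allowance counts patients who do not receive their allocated pacing as lost, but the intention-to-treat analysis keeps them, so the stated 80% power does not follow from 470 patients

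*Protocol article*

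**What the plan says.** All references are to the protocol article.

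- **Sample size calculation.** The proportion of RVP patients with a primary endpoint event "before 1-year follow-up will be at least 25" per cent. For the other arm: "We expect an event rate of 14% for the LBBAP group". From these rates: "To achieve a power of 80% at the 5% level of significance, 203 patients per group, or 406 in total, would be needed". The last step is: "Accounting for around 15% loss to follow-up or patients not receiving the allocated intervention, 470 patients are needed". The same section says that the LBBAP effect was taken to equal that of His bundle pacing.
- **Statistical analyses.** "Analyses will be executed on an intention-to-treat population. This population includes all patients who are randomized, regardless of the treatment they received". The section adds that LBBAP patients who end up with right ventricular or His pacing count as LBBAP, and that the same rule applies to RVP patients who do not receive RVP. The per-protocol analysis is secondary and exploratory.
- **Intervention group.** If the lead cannot be positioned in the LBBAP region, "the lead may be placed at the His bundle region or in the right ventricle according to the physician’s discretion".

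**The concern.** Loss and non-receipt act on power in different ways. A patient with no outcome reduces the number analysed and leaves the expected difference alone, so dividing by (1 − loss) restores the power. A patient who is analysed in the LBBAP arm but paced in the right ventricle still counts towards the number analysed, and moves that arm's event rate towards the control rate. Adding patients one for one does not make up for this, because the required number rises roughly with the inverse square of the remaining difference.

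The sample size section uses one head-count allowance for both and leaves 25% against 14% unchanged. The analysis section then keeps the non-receivers. The 80% therefore belongs to an analysis that drops them, which is not the primary analysis. At stake is how a neutral result is read: it would be taken to come from a trial with 80% power when the intention-to-treat power could be several points lower.

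**Working it through.** **Inputs from the article.** RVP rate p1 = 0.25; LBBAP rate p2 = 0.14; 5% level; 80% power; 1:1 allocation; allowance of around 15%; 470 randomized, so 235 per arm. Sidedness is not stated. Two-sided testing reproduces the article's number, whereas one-sided testing would give 160 per arm.

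**Step 1: reproduce 406.** With pooled variance, no continuity correction and p̄ = (p1 + p2)/2 = 0.195:

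n = [1.96·√(2p̄(1−p̄)) + 0.8416·√(p1(1−p1) + p2(1−p2))]² / (p1−p2)²
= (1.0982 + 0.4670)² / 0.11² = 202.5, so 203 per arm and 406 in total. This agrees.

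**Step 2: reproduce 470.** 406 × 1.15 = 467 and 406 / 0.85 = 478. The figure of 470 lies between them and corresponds to 1 − 406/470 = 13.6% removed. So the whole allowance was handled as removed patients, with both event rates unchanged.

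**Step 3: power when non-receivers are kept.** Let L be the loss in each arm, c the share of the LBBAP arm not receiving LBBAP, and f the fraction of those paced in the right ventricle. Assumptions:

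- L + c = 15%.
- Right ventricular fallback carries the 25% risk.
- His fallback carries the 14% risk, following the article's equal-effect assumption.
- There is no crossover in the RVP arm.

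Then m = 235(1 − L) per arm, p2* = 0.14 + 0.11·c·f, and with p̄ now the mean of p1 and p2*:

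power = Φ{[√m·(p1 − p2*) − 1.96·√(2p̄(1−p̄))] / √(p1(1−p1) + p2*(1−p2*))}

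Example with L = 5%, c = 10%, f = 1: m = 223.25, p2* = 0.151, difference 0.099. The numerator is 1.4792 − 1.1098 and the denominator 0.5619, so z = 0.658 and power is 74.5%.

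| Loss / non-receipt | All to right ventricle (f = 1) | Half to His (f = 0.5) | All to His (f = 0) |
|---|---|---|---|
| 15% / 0% | 79.5% | 79.5% | 79.5% |
| 10% / 5% | 77.2% | 79.5% | 81.7% |
| 7.5% / 7.5% | 75.9% | 79.5% | 82.7% |
| 5% / 10% | 74.5% | 79.4% | 83.7% |
| 0% / 15% | 71.3% | 79.1% | 85.5% |

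With no loss and no crossover, 235 per arm give 85.5%. A 15% loss therefore costs about 6 points (to 79.5%), while 15% retained at the RVP risk costs about 14 (to 71.3%).

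**Step 4: where 80% still holds at 470.** With crossover from LBBAP to right ventricular pacing only, 80% is kept up to about 6.5% crossover with no loss, or about 4.3% with 5% loss.

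**The case against.** Several points on the other side are sound.

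- **His fallback need not dilute.** The article allows it and assumes the two effects are equal. A reader might infer from the first column of the table that any split of the 15% leaves the trial below 80%. The documents do not support that: with all fallback to His pacing, power is 81.7% to 85.5% once non-receipt is 5% or more.
- **Crossover in both arms.** Equal crossover of 5% to 15% in each arm would give about 73% down to 56%. The article allows for RVP patients not receiving RVP but gives no rate, and it describes no fallback from RVP to LBBAP. Those figures are illustrative at most and are not part of this point.
- **470 or 478.** A reader might see a second arithmetic error in multiplying rather than dividing. With an allowance of around 15%, 470 is within rounding, and 15% pure loss still gives 79.5%.
- **Multiple imputation.** A patient missing only the 1-year echocardiogram stays in the primary analysis, so loss may cost less than full removal. The article does not quantify this, and imputation cannot undo dilution by crossover.
- **The 25% is a floor.** Keeping the same relative effect (0.14/0.25 = 0.56), an illustrative control rate of 28% gives 80.4% at 5% loss and 10% right ventricular fallback. But the article claims its power at 25%.
- **The Limitations section calls the calculation an estimation.** It attributes the uncertainty to limited data on event rates and effect size, and does not mention dilution.

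These points bear on the size of the shortfall, and some of them could remove it. They do not reconcile the allowance with the analysis population.

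**Conclusion.** The point stands as an inconsistency between the sample size section and the intention-to-treat rule; it should be fixed. The 80% is derived as if non-receivers leave the analysis, and they do not. Across a 15% allowance with 5% to 15% non-receipt confined to the LBBAP arm, power at 470 runs from 77.2% down to 71.3% if all fallback is right ventricular. It is about 79% if half is His pacing, and about 82% to 86% if all is. Any RVP-arm crossover to LBBAP lowers these figures. The result rests on two quantities that the article does not give, the split between loss and non-receipt and the fallback mix, and on the assumption that crossovers take the full risk of the pacing they receive.

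A reader might conclude that the trial is shown to be underpowered or must enrol more patients. The documents support neither. What they show is that the stated power has not been derived for the planned analysis. The endpoint, the analysis population and the test are unaffected.

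**What to change.** Rewrite the last step of the sample size paragraph:

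1. State four planning values separately: loss to follow-up, right ventricular fallback in the LBBAP arm, His fallback in the LBBAP arm, and RVP-arm crossover to LBBAP.
2. Apply the diluting crossovers to the event rates of the intention-to-treat comparison. Say that His fallback is treated as non-diluting because the effects are assumed equal, or show the power without that assumption.
3. Divide by (1 − loss) for loss only.
4. Restate the power at 470, with a short range if the planning values are uncertain.

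An illustration of the form, with placeholder values: assuming 5% loss, 10% of the LBBAP arm paced in the right ventricle and no other crossover, 470 patients give 74.5% power for 25% against 14% under full adherence; with 5% loss, 80% power holds up to about 4.3% such crossover.

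The cost is wording only, with no added enrolment and no change to the analysis or to clinical management. The downside is that the stated power may become less favourable.

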### Statistical analyses

Analyses will be executed on an intention-to-treat population. This population includes all patients who are randomized, regardless of the treatment they received. For example, all patients randomized to LBBAP and not receiving LBBAP (i.e. RVP or HBP) will be analysed according to their randomization group (thus LBBAP). The same counts for all patients randomized to RVP and not receiving RVP.

Given the possibilities of crossovers, as a secondary analysis, an exploratory per-protocol analysis will be performed to check for consistency and explore potential efficacy. The per-protocol analysis will include all patients randomized to LBBAP who received LBBAP and all patients randomized to RVP who received RVP.

The ECG corelab will assess all paced baseline and 1-year follow-up ECGs to determine the pacing type the patients are treated with. Descriptive statistics (i.e. count (%)) will be used to display the actual pacing types (i.e. RVP, LBBAP, or HBP) in both treatment groups.

Categorical baseline characteristics will be presented as count (percentage). Continuous characteristics will be presented as mean (± standard deviation) or median (interquartile range) as appropriate.

All primary and secondary study endpoints will be described in detail as count and percentage (binary endpoints), using Kaplan–Meier curves (time-to-first occurrence of an endpoint), Cox regression analysis, and as mean and standard deviation (continuous endpoint, i.e. LVEF), depending on the type of outcome. All null-hypothesis testing will be performed using a level of significance of α = 0.05.

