**Figure 1 oeag108-F1:**
[figure not shown]
Trial design. PM, pacemaker; LBBAP, left bundle branch area pacing; RVP, right ventricular pacing; TTE, transthoracic echocardiogram. *TTE was only performed at baseline and 12 months follow-up.

**Table 1 oeag108-T1:** Inclusion and exclusion criteria of the LEAP study

Inclusion criteria	Exclusion criteria
Age ≥ 18 years Life expectancy with good functional status of ≥ 1 year Class I or IIa PM indication due to AV conduction disorder Acquired third or second degree AVB Atrial arrhythmia with slow ventricular conduction Expected VP percentage ≥ 20% LVEF ≥40% on TTE ≤ 3 months before PM implantation Signed and dated ICF	HF NYHA classes III and IV Class I indication for CRT Class I indication for ICD Previous implanted CIED (except for ILR) Atrial arrhythmia with planned AV junction ablation ACS or unstable angina PCI or CABG ≤30 days before enrollment VHD with indication for valve repair or replacement HCM with IVS thickness > 2 cm
	Renal insufficiency requiring HD Active infectious disease or malignancy Pregnancy

ACS, acute coronary syndrome; AV, atrioventricular; AVB, atrioventricular block; CABG, coronary artery bypass graft; Class I, pacemaker implantation is indicated^19^; CIED, cardiac implantable electronic device; Class IIa, pacemaker implantation should be considered^19^; CRT, cardiac resynchronization therapy; HCM, hypertrophic cardiomyopathy; HD, haemodialysis; HF, heart failure; ICD, implantable cardioverter defibrillator; ICF, informed consent form; ILR, implantable loop recorder; IVS, interventricular septum; LVEF, left ventricular ejection fraction; NYHA, New York Heart Association classification; PCI, percutaneous coronary intervention; PM, pacemaker; VHD, valvular heart disease; VP, ventricular pacing.

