### Statistical analyses of the secondary endpoint

For the secondary endpoints, the treatment groups will be compared using Cox proportional hazards regression, again adjusted for the stratification variables used in the randomization procedure. The secondary endpoints are analysed without corrections for multiplicity. Hazard ratios will be presented with associated 95% confidence interval. The proportional hazards assumption will be tested as the association between the scaled Schoenfeld residuals and follow-up time. Change in LVEF will be compared between groups using multivariable linear regression analysis. We will use multivariable generalized linear regression analysis with a link-function dependent on the specific distribution to assess between-group differences in diastolic function.

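### Kaplan–Meier curves for heart-failure hospitalisation alone and for new AF will overstate absolute risk, because death is a competing event that the stated method can only censor

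*Protocol article*

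**What the plan says.** In the protocol article, the section Statistical analyses sets the descriptive method by type of outcome. Time-to-first endpoints are described "using Kaplan–Meier curves (time-to-first occurrence of an endpoint"), together with Cox regression.

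The section Secondary endpoints lists, as separate items, "Time to first occurrence of hospitalization for heart failure" and "Time to first occurrence of AF *de novo* and AF burden at every follow-up visit". Neither includes death. The same list has all-cause mortality on its own and "Time to first occurrence of all-cause mortality or hospitalization for heart failure", which does count death. Individual follow-up for these endpoints runs from 1 year to 36 months.

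For the comparison between arms, the section on secondary endpoint analysis states: "For the secondary endpoints, the treatment groups will be compared using Cox proportional hazards regression". Adjustment is for the stratification variables. The article does not mention competing risks, cumulative incidence functions or the handling of deaths in the endpoints that exclude death.

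Two further statements bear on AF. Table 1 admits patients with "Atrial arrhythmia with slow ventricular conduction", and the general population statement is "Analyses will be executed on an intention-to-treat population".

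**The concern.** A patient who dies can no longer be hospitalised for heart failure or develop AF. A Kaplan–Meier curve for such an endpoint has to treat the death as censoring, as if the patient remained at the same future risk as survivors. One minus the curve then estimates the risk in a hypothetical population without death, which is at least as high as the share of patients who actually have the event.

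Death is not incidental here: it is a component of the primary composite, which the trial hypothesises LBBAP will reduce. If mortality differs between arms, the overstatement differs too. Equal Kaplan–Meier curves could then sit on top of unequal actual incidences, or the reverse. What is at stake is how the absolute risks for two secondary endpoints are read, mainly late in follow-up.

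**Working it through.** **The plan's own figures.** The article gives no expected rate for death, heart-failure hospitalisation or AF separately, so there is no figure of its own to reproduce for these endpoints. Its sample size concerns the binary primary endpoint. That size reproduces at 203 per group (25% v 14%, two-sided 5%, 80% power, pooled variance) and this point does not touch it. All rates below are assumptions.

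**Formulas.** Take constant cause-specific hazards, *h* for the event and *d* for death, over *t* years:

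- one minus Kaplan–Meier, deaths censored: 1 − exp(−*h t*)
- actual cumulative incidence: *h*/(*h* + *d*) × [1 − exp(−(*h* + *d*) *t*)]

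**Heart-failure hospitalisation, wide range.** Annual risks of 3–10% for each cause, converted by hazard = −ln(1 − annual risk):

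| Annual death | Annual HF hospitalisation | Years | 1 − KM | Actual | Excess (points) |
|---|---|---|---|---|---|
| 3% | 3% | 1 | 3.00% | 2.96% | 0.05 |
| 5% | 5% | 1 | 5.00% | 4.88% | 0.13 |
| 10% | 10% | 1 | 10.00% | 9.50% | 0.50 |
| 3% | 3% | 3 | 8.73% | 8.35% | 0.38 |
| 5% | 5% | 3 | 14.26% | 13.25% | 1.02 |
| 10% | 10% | 3 | 27.10% | 23.43% | 3.67 |

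Excesses are taken before rounding. Across the range they are 0.05–0.5 points at 1 year and 0.4–3.7 points at 3 years.

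**New AF at 3 years.** Here the rates are used directly as hazards, with *h* = 0.10:

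- *d* = 0.08: 1 − exp(−0.30) = 25.9%, against (0.10/0.18) × [1 − exp(−0.54)] = 23.2%. Excess 2.7 points.
- *d* = 0.12: 25.9%, against (0.10/0.22) × [1 − exp(−0.66)] = 22.0%. Excess 4.0 points.

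**Between arms at 3 years.** Give both arms the same heart-failure hazard and let only death differ:

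- *h* = 0.05, *d* = 0.05 v 0.10: both Kaplan–Meier curves read 13.9%; the actual incidences are 13.0% and 12.1%, about 0.9 points apart.
- *h* = 0.08, *d* = 0.05 v 0.10: both curves read 21.3%; the actual incidences are 19.9% and 18.5%, about 1.3 points apart before rounding.

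For scale, with 470/2 = 235 patients per arm and a risk near 13%, the standard error of a difference is about √(2 × 0.13 × 0.87/235) = 3.1 points, ignoring censoring.

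**The case against.** **The effect is small and presentational.** The comparative result is a Cox hazard ratio. With deaths censored, it is a valid cause-specific hazard ratio. The 3-year figures sit at the maximum follow-up, where few patients may still be at risk; at 1 year the excess for heart-failure hospitalisation is at most about 0.5 points. Even a doubling of mortality hides only about 1 point between arms, well inside sampling error. Mortality and death-or-heart-failure hospitalisation are reported separately, so a mortality difference would be visible. All of this stands and limits the weight of the point. It does not correct the two curves themselves: the method is stated, and following it produces the overstatement.

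**Patients already in AF.** A reader might infer that they will be counted in the de novo analysis, since atrial arrhythmia is an eligibility route and the population is defined as follows: "This population includes all patients who are randomized, regardless of the treatment they received". If 10–40% had AF at entry (an assumption) and stayed in the denominator, a true 20% risk would show as (1 − 0.10) × 20% = 18% down to (1 − 0.40) × 20% = 12%. The article does not support the inference. That sentence and its examples concern allocation and crossover, the term de novo points the other way, and the at-risk definition may stand in the full protocol, the analysis plan or the adjudication charter, none of which is shown. Only a request for confirmation is justified.

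**Costs.** A reader might also infer that misstated risks carry into the economic evaluation. The article takes resource use from case record forms and questionnaires. The budget impact analysis includes heart-failure costs but names no Kaplan–Meier input. No link is shown.

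**Conclusion.** The concern holds for two secondary endpoints. For heart-failure hospitalisation alone and for AF de novo, the stated Kaplan–Meier description overstates actual cumulative incidence whenever patients die first. The size is negligible to small at 1 year and modest at 3 years. It rests on constant hazards and assumed rates, because the article provides none; the ranges would move with the trial's real mortality.

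It would go too far to say that the trial's reported incidences will be wrong in general. The curves for all-cause death and for death or heart-failure hospitalisation are unaffected by this problem, as are the primary logistic analysis and the Cox comparisons. The composition of the AF risk set is a matter for clarification, not an established error.

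**What to change.** For first heart-failure hospitalisation and first AF de novo, present Aalen–Johansen cumulative incidence curves by arm with death as the competing event. Keep the adjusted Cox model for both, label its result a cause-specific hazard ratio, and show it beside the mortality hazard ratio. Keep Kaplan–Meier for all-cause death and for death or heart-failure hospitalisation.

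As a clarification, confirm that the AF de novo analysis is restricted to patients without AF before or at baseline.

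The cost is a few sentences in the analysis plan before analysis and standard software. No extra patients, follow-up or change to the primary analysis is needed.
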